## **Serious Adverse Event (SAE) Reporting**

In order to comply with current regulations on serious adverse event reporting to Health Authorities the investigator pledges to document accurately the event, to respect notification deadlines, to provide the Sponsor with all necessary information and, if requested by the sponsor, to give access to source documents. The investigator should complete the SAE form provided by the sponsor (Oxford University) and report any SAE within 24hours using the email address [[contact]](mailto:[contact]) .

All SAEs will be reported by telephone, or email or fax to the local safety monitor and through her/him to the sponsor, the Research Ethics Committee of Oxford University and the Conseil National de Recherche en Santé, within one working day of the investigator becoming aware of the SAE occurrence.

Only suspected unexpected serious adverse reactions will be sent to the Medicines and Healthcare Products Regulatory Agency (MHRA) of the United Kingdom and this will be done within 7 days. The sponsor pledges to inform the Authorities of any trial discontinuation and specify the reason for discontinuation.

## **Adverse Event Monitoring**

### **Local Safety Monitor**

A Local Safety Monitor (LSM) will be appointed to provide real-time safety oversight. The LSM will review SAEs immediately after they occur and follow these events until resolution. The LSM has the power to terminate the study if deemed necessary following a SAE.

*Reference safety parameters that are outcome measures (Section 10)*

## **Methods and Timing for Assessing, Recording, and Analyzing Safety Parameters**

The following scale will be used to assess the severity of all AEs:

- 0 = Absence of the indicated symptom
- 1 = Mild (awareness of a symptom but the symptom is easily tolerated)
- 2 = Moderate (discomfort enough to cause interference with usual activity)
- 3 = Severe (incapacitating; unable to perform usual activities; requires absenteeism or bed rest)
- 4 = Life-threatening

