**Days 1–6 post vaccination (+/- 0 day)**

- An interim history will be taken and, if considered necessary a physical examination emphasizing any acute complaints will be performed. Vital signs will be checked and documented
- The injection site will be inspected and the largest diameter of any hardness or redness present, as well as the degree of pain reported for the time of the visit will be documented into the CRF.
- Solicited adverse events (local and general) that may have occurred since the vaccination will be documented in the CRF.

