### Definitions

#### Adverse Event

An AE is any untoward medical occurrence, including a dosing error, which may occur during or after vaccination.

The AE may or may not have a causal relationship with vaccination as indicated by physical signs, symptoms, and/or clinically significant laboratory abnormalities that occur. The definition includes intercurrent illnesses, injuries, exacerbation of pre-existing conditions, and events occurring as a result of product misuse or overdose.

A change in a laboratory variable is considered an AE if it leads to a change in the subject's functional status or if it is considered by the attending physician to be clinically significant. The following laboratory studies will be monitored during the course of this study (as previously outlined): full blood count (FBC), urea, creatinine, ALT, total bilirubin, albumin, alkaline phosphatase, sodium and potassium.

Adverse events will be graded and reported as detailed below.

Expected local reactions to the vaccine will not be recorded as an adverse event, but will be recorded on the CRFs. These include:

- Redness
- Swelling
- Pruritus
- Scaling
- Localised pain

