## **10 STATISTICAL CONSIDERATIONS**

### **Determination of the Sample Size**

This is an observational and descriptive safety study, where 24 subjects will be vaccinated. This sample size should allow determination of the magnitude of the outcome measures, especially of serious and severe adverse events, rather than aiming to obtain statistical significance.

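### The single severity scale set for all AEs cannot grade a symptom-free laboratory AE as moderate or severe, so the severe-AE proportion can be understated

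*Protocol*

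**What the plan says.** All of this is in the Protocol.

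- **Severity scale** (section 8, Methods and Timing for Assessing, Recording, and Analyzing Safety Parameters): "The following scale will be used to assess the severity of all AEs". The lowest grade on it reads "0 = Absence of the indicated symptom". Grade 1 is a symptom that the subject notices but tolerates well, and grade 2 is discomfort that gets in the way of normal activity. The severe grade reads "3 = Severe (incapacitating; unable to perform usual activities; requires absenteeism or bed rest". The top grade, 4, is life-threatening, with no further wording.
- **AE definition** (section 8, Adverse Event): a laboratory change is an AE on either of two grounds. One is a change in functional status. The other is "if it is considered by the attending physician to be clinically significant". The tests listed for monitoring are the FBC and eight biochemistry analytes (urea, creatinine, ALT, total bilirubin, albumin, alkaline phosphatase, sodium, potassium). The text then sends the reader onward for grading, and the scale above is the only one that follows.
- **Abnormal laboratory values** (section 8): the text provides for repeat tests and tests of causality. It gives no grades or thresholds.
- **Purpose of the sample size** (section 10, repeated in section 3): 24 subjects should allow the magnitude of the outcome measures to be determined, "especially of serious and severe adverse events".

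**The concern.** AEs are the primary outcome, and severe AEs are named as a quantity of particular interest. The protocol defines severe only through this scale. If one class of AE cannot reach the severe grade by construction, the reported severe proportion leaves that class out without saying so. Grades for clinical and laboratory events then do not mean the same thing.

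This is a rule that the protocol states, not a detail left for the SAP. Investigators assign severity during the trial using this scale. An SAP that graded laboratory AEs by their values would contradict the protocol rather than complete it.

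**Working it through.** The protocol gives no severe-AE rate, laboratory-event rate, power or precision target, so there is no figure of its own to reproduce. The check is a reading of the text followed by an illustration of size.

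**Step 1. Can a laboratory AE exist without symptoms?** Yes. The two grounds in the AE definition are alternatives, and the clinical-significance ground requires no symptom and no functional change.

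**Step 2. Which grade does the scale give it?** Take a laboratory AE declared on clinical significance alone, with no symptom, no functional change and no threat to life.

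| Grade | What it requires | Met? |
|---|---|---|
| 0 | symptom absent | yes |
| 1 | awareness of a symptom | no |
| 2 | discomfort that interferes with activity | no |
| 3 | incapacity, absence from work or bed rest | no |
| 4 | threat to life | no, by assumption |

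The literal grade is 0, and the size of the abnormality plays no part. This contradicts itself: the event is clinically significant enough to be an AE, yet has severity zero.

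**Step 3. Which laboratory AEs are not affected?** Those declared through a change in functional status can be graded by the activity wording of grades 2 and 3. Those that threaten life can be graded 4.

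**Step 4. Illustrative size.** Inputs: n = 24 overall (section 10) and 12 per group (Protocol Summary). The number of affected subjects, x, is an assumption, shown from 1 to 3. Each affected subject is assumed to have no other severe AE, and no other subject to have one. The value-based column also assumes that the table would grade these events severe.

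Exact (Clopper-Pearson) 95% limits: lower = Beta quantile 0.025 with parameters (x, n − x + 1); upper = Beta quantile 0.975 with parameters (x + 1, n − x). For x = 0 the lower limit is 0 and the upper limit is 1 − 0.025^(1/n):

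- n = 24: 1 − 0.025^(1/24) = 14.2%
- n = 12: 1 − 0.025^(1/12) = 26.5%

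| Affected subjects | Scale as written | Value-based laboratory grading |
|---|---|---|
| 1 of 24 | 0/24 = 0% (0 to 14.2%) | 1/24 = 4.2% (0.1 to 21.1%) |
| 2 of 24 | 0/24 = 0% (0 to 14.2%) | 2/24 = 8.3% (1.0 to 27.0%) |
| 3 of 24 | 0/24 = 0% (0 to 14.2%) | 3/24 = 12.5% (2.7 to 32.4%) |
| 1 of 12 (one group) | 0/12 = 0% (0 to 26.5%) | 1/12 = 8.3% (0.2 to 38.5%) |

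Each affected subject shifts the point estimate by 1/24 = 4.2 percentage points overall, or 1/12 = 8.3 points within a group. The intervals show the uncertainty at these sample sizes; they do not measure bias.

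**The case against.** The strongest reply is that little depends on the grade. A marked laboratory abnormality is still recorded as an AE, can be retested, and is followed until it resolves or a non-study cause is assigned. It can also qualify as an SAE under the important-medical-event criterion, which names blood dyscrasias. The Local Safety Monitor reviews SAEs and the halting rule is triggered by a SUSAR, so both turn on seriousness, not on severity. The analysis is descriptive only. All of this stands, and it confines the problem to the reported severity distribution.

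A second reply is that grade 0 for a declared AE is so plainly unintended that investigators would not apply it. That may be so. But they would then be grading without a stated rule, which is no better for a primary outcome.

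Three stronger readings are tempting and are not supported:

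- **That the scale rests on symptoms throughout.** Grade 4 carries no symptom wording, and functional change is a gradable route to a laboratory AE. The gap is at grades 2 and 3, for AEs declared on clinical significance alone.
- **That local reactions are misgraded too, because the "largest diameter of any hardness or redness present" is measured but not used in the scale.** The AE definition says that expected local reactions, redness and swelling among them, are not recorded as AEs. The scale therefore does not govern them, and the diameters are already in the CRF to be summarised as measured.
- **That every scheduled laboratory result is ungradable.** The scale grades AEs, not values, and a value must first be declared an AE. A count of planned tests would also assume that every subject receives the second dose, which Group 1 subjects may decline and which the eligibility recheck before that dose can prevent.

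**Conclusion.** The point holds in a limited form. As written, a symptom-free laboratory AE that is not life-threatening meets grade 0 and cannot be moderate or severe, so the severe-AE proportion can be understated. The size cannot be derived from the protocol, because the number of such events is unknown and may be zero. One subject whose only severe event is of this kind changes 0/24 (0 to 14.2%) to 1/24 = 4.2% (0.1 to 21.1%).

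A reader might infer that safety oversight is weakened. The documents do not support that: event capture, SAE reporting and halting do not depend on the grade.

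The conclusion assumes that the scale is applied literally and that no value-based laboratory grading stands elsewhere in force; the protocol contains none and refers to none. It is worth correcting because the primary outcome is affected and the values needed are already collected.

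**What to change.** Amend section 8 in two places.

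1. State that the existing scale applies to clinical (symptomatic) AEs only.
2. State that laboratory AEs for the FBC and the eight biochemistry analytes are graded by a named, versioned toxicity table with numeric cut-offs. Apply it to the recorded values in both groups, including subjects already enrolled, so that the groups are graded alike.

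No new data are needed. The cost is a protocol amendment with sponsor agreement and prior ethics approval, as the Protocol Deviations text in section 14 requires, plus some retrospective regrading, because Group 1 recruitment preceded this version. The safety tables may look slightly less favourable, since some laboratory AEs would then count as moderate or severe.

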## **Reporting of Pregnancy**

All subjects will be required to be using a reliable method of barrier contraception (i.e., condoms) prior to study enrolment, for the whole duration of the study and for 3 months after the last follow-up visit. A pregnancy test (urine) will be performed on each female subject on vaccination day. Should a subject become pregnant during the trial, she will be followed according to the protocol but in addition will be followed until pregnancy outcome.

**Procedures to be Followed in the Event of Abnormal Laboratory Test Values or Abnormal Clinical Findings**

Any subject with a clinically significant finding (e.g. hypertension) or abnormal biochemical or haematological may have the test repeated to ensure this was not a single occurrence prior to inclusion. If the test remains clinically significant the subject will be excluded from the study and referred to their HIV physician or GP as appropriate for further investigation and management with the permission of the volunteer. If occurring during the trial, tests may be repeated to verify the results, and further tests may be instigated to establish causality. The volunteer will be kept informed of all such occurrences and advised of actions to be taken, and their verbal/written consent taken for extra tests where appropriate.

**Halting Rules**

Any SUSAR will result in suspension of the trial until a safety review is convened.

## 9 CLINICAL MONITORING STRUCTURE

**Local monitor: [name] [name]**

**Independent monitor: [name], Appledown**

*This section will describe the study monitoring to be conducted to ensure the safety and conduct of the study complies with 45 CFR 46, GCP and ICH Guidelines, DMID and other sponsor collaborator's guidelines, as appropriate.*

### **Site Monitoring Plan**

#### **Set-up Visit**

A set-up visit will be performed before the inclusion of the first subject in the study. The Monitor will verify and document that the material to be used during the trial has been received and that the investigational team has been properly informed about the trial, regulatory requirements, and the SOPs.

#### **Follow-up Visits**

The Monitor will carry out regular follow-up visits. The investigator will be available for these visits and to allow the monitoring staff direct access to subject medical file and CRFs. The Monitor is committed to professional secrecy.

During the visits, the Monitor will:

- carry out a quality control of trial progress: respect of protocol and operating guidelines, data collection, signature of consent forms, completion of document and appearance of SAE,
- sample and product management, cold chain monitoring,
- collect the CRFs and correspondent correction sheets,
- assess the inclusions in order to evaluate the number of complete or on-going observations.

The Monitor will discuss any problem with the investigator and define with him the actions to be taken.

Once the CRFs corresponding to the last visit have been returned duly completed and signed, the investigator must be available to complete the correction sheets transmitted by the Monitor, if necessary, until the database is locked.

### **Close-out Visit**

A close-out visit will be performed at the end of the trial. Its goals are to make sure that:

- The centre has all the documents necessary for archiving,
- All paperwork is satisfactorily completed

### **Audits and Inspections**

If necessary, a quality assurance audit will be carried out by independent auditors to make sure that the trial has been conducted according to the protocol and the applicable regulations.

An inspection may be conducted by Regulatory Authorities. The investigator must allow direct access to trial documents.

## **10 STATISTICAL CONSIDERATIONS**

### **Determination of the Sample Size**

This is an observational and descriptive safety study, where 24 subjects will be vaccinated. This sample size should allow determination of the magnitude of the outcome measures, especially of serious and severe adverse events, rather than aiming to obtain statistical significance.

### **Statistical Methods**

The analysis will be only descriptive, as the sample size does not allow to perform comparison.

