## Rationale

This study is designed to evaluate the safety of MVA85A in healthy volunteers in Senegal who are infected with HIV. In phase I studies, a single vaccination with MVA85A, when administered at a dose of  $5 \times 10^7$  pfu intradermally, has been shown to be safe in both mycobacterially naïve individuals, those previously vaccinated with BCG and latently infected individuals. We will use  $1 \times 10^8$  pfu MVA85A intradermally in this study. A trial in BCG vaccinated subjects showed that the higher dose ( $1 \times 10^8$  pfu MVA85A) induced a significantly higher immune response but did not have a higher AE profile. In addition, because of a variable immune response, the trial in HIV positive subjects in the UK is split into two groups, the first getting  $5 \times 10^7$  pfu and the second getting  $1 \times 10^8$  pfu MVA85A. It has, therefore, been decided to use the higher dose in order to maximise the immune response whilst maintaining a good safety profile.

However, the T cell immunogenicity of MVA85A in HIV infected subjects who are not on ARV treatment is reduced compared to previous trials in HIV negative subjects.

There are two potential interventions we can do to improve the immunogenicity in this important target population where TB incidence is very high. First, it is possible that the immune response to MVA85A would be better in healthy, asymptomatic people who have a CD4 count of more than 300, but who have had their immune response reconstituted by ARV therapy. Therefore the rationale for adding a second arm to this study is to investigate the immunogenicity in a group of HIV infected subjects who are stable on ARV treatment.

It is important to determine which subjects have the best immune response to this vaccine, in order to select this group for inclusion in a proof-of-concept efficacy trial; this would maximize the prospects of demonstrating efficacy in this important target population.

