### **Secondary:**

To assess the immune responses induced by two vaccinations with MVA85A in healthy subjects who are infected with HIV, including the boosting affect of second MVA85A vaccination

To compare the immune response between subjects who are and who are not on ARVs after vaccination with MVA85A

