#### **Sample size:**

This is an observational and descriptive safety study, 24 subjects will be recruited from HIV clinics and vaccinated with MVA85A. Half of the subjects will not have started on ARVs and half will be stable on ARVs. This sample size should allow determination of the magnitude of the outcome measures, especially of serious and severe adverse events, rather than aiming to obtain statistical significance.

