## 5 STUDY ENROLLMENT AND SCHEDULE OF FOLLOW-UP VISITS

Subjects who match all inclusion and exclusion criteria and who are available for the follow up will be invited to take part after screening. Subjects will attend the Bacteriology and Virology Laboratory at Le Dantec Teaching Hospital for vaccination. All volunteers will be vaccinated with MVA85A and will not be randomised.

The following table illustrates the sequence of events from screening, through vaccination (day 0) and subsequent follow-up visits (explained in more detail in the text that follows):

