#### **Secondary:**

To assess the effect of vaccination with MVA85A in healthy subjects who are infected with HIV on the immune response to antigen 85A (the antigen in the vaccine) and to ESAT-6 and CFP-10 (markers of TB infection).

The effect of a booster vaccination at six months will also be assessed.

A comparison between the immune responses by HIV-infected people who are not and are on ARVs will also be done.

The specific endpoints for immunogenicity will be markers of cell-mediated immunity as outlined below:

- Ex-vivo Elispot assay for interferon gamma: (exploratory immunology)

In all previous TB vaccine trials this has been the main immunological readout. However, there are as yet no validated cellular immunological assays and no perfect correlate of protection has been identified for TB. There is therefore ongoing work in the laboratory to develop other cellular assays including flow cytometry tests.

In view of this, other immunological assays may include:

- ex-vivo elispot assays for interleukin-2 and tumour necrosis factor alpha
- cultured elispot
- T cell proliferation
- whole blood assay for interferon-gamma
- T cell depletion assays
- cytokine detection using ELISA/LUMINEX or
- intracellular staining and FACScan analysis will be performed at the discretion of the investigators. (This also includes gene expression studies.)
- any other immunological assays that are developed during the timeline of the trial

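### The protocol commits to comparing immune response by ARV status, but its statistics section says no comparison can be made; the sample size limits testing, not estimation

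*Protocol*

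**What the plan says.** **Commitments to compare.** Section 2, Secondary, lists as an objective "To compare the immune response between subjects who are and who are not on ARVs after vaccination with MVA85A", and the Protocol Summary repeats it. Section 7, Secondary, states it as a task: "A comparison between the immune responses by HIV-infected people who are not and are on ARVs will also be done".

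**What the comparison is for.** The Rationale in section 1 explains why the ARV arm was added: "It is important to determine which subjects have the best immune response to this vaccine, in order to select this group" for a proof-of-concept efficacy trial.

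**The boost.** Section 2 also asks for an assessment of the responses to two vaccinations, "including the boosting affect of second MVA85A vaccination". Section 7 likewise says the effect of the booster will be assessed. The verb is assess, not compare.

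**The statistics section.** Section 10, Determination of the Sample Size, says "This is an observational and descriptive safety study, where 24 subjects will be vaccinated" and disclaims any aim of statistical significance. Statistical Methods then consists of one sentence: "The analysis will be only descriptive, as the sample size does not allow to perform comparison".

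**Design facts.** Section 3 gives the split: "Half of the subjects will not have started on ARVs and half will be stable on ARVs", that is 12 and 12. Section 5 says "All volunteers will be vaccinated with MVA85A and will not be randomised".

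**The concern.** A secondary objective and an outcome section promise a contrast that the statistics section calls impossible. This is not detail that can be left to a statistical analysis plan, because no plan can both make the comparison and accept that none can be made.

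If the statistics section is followed literally, the two groups are summarised side by side with no estimate of the difference and no interval. The question that motivated the second arm then has no quantified answer, although the Rationale expects it to inform who enters an efficacy trial. If the objectives are followed instead, the comparison is made against a protocol statement that the data cannot bear it.

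**Working it through.** **1. Where the texts conflict**

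| Place in the protocol | ARV versus no ARV | Second dose |
|---|---|---|
| Section 2, Secondary | to be compared | to be assessed |
| Section 7, Secondary | comparison will be done | to be assessed |
| Section 1, Rationale | basis for selecting a group | a way to enhance immunogenicity |
| Section 10, Statistical Methods | no comparison possible | descriptive only |

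For the ARV contrast the conflict is explicit. For the boost it is only implied: judging a boost means setting values after the second dose against earlier ones, but the text does not use the word compare.

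**2. What 12 per group can do**

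The total of 24 is stated without alpha, power, effect size or SD, so there is no derivation to reproduce. Assumptions here: two-sided alpha 0.05, 80% power, equal SDs, all 12 per group evaluable, differences in units of the between-subject SD.

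- Standard error of the difference: √(2/12) = 0.408 SD.
- Detectable difference, normal approximation: (1.960 + 0.842) × 0.408 = 1.14 SD. With noncentral-t power it is 1.20 SD.
- Power at a true difference of 0.5 SD: 22% (t) or 23% (normal). At 0.8 SD: 47% or 50%. At 1.0 SD: 65% or 69%.
- 95% CI half-width: t(22, 0.975) × 0.408 = 2.074 × 0.408 = 0.85 SD.

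To put the half-width on a fold scale an SD must be assumed, since the protocol gives none. If the SD of log10 ELISPOT is 0.3, the ratio is known to within a factor of 10^(0.847 × 0.3) = 1.8; if 0.6, 10^(0.847 × 0.6) = 3.2.

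**3. What the paired data can do for the boost**

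Units here are SDs of the within-subject difference, so these figures are not on the same scale as those in step 2. The 95% CI half-width is t(n−1, 0.975)/√n.

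| Paired n | 95% CI half-width | Detectable at 80% power |
|---|---|---|
| 24 | 2.069/√24 = 0.42 | 0.60 |
| 12 | 2.201/√12 = 0.64 | 0.89 |

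The paired n may fall below 24. The Rationale makes the second dose voluntary for Group 1 subjects already recruited, and Booster vaccination (section 5) has those attending visit 12.1 re-screened before it.

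**4. Which pre-boost sample exists**

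Table 3 schedules research bloods at Day 168 but none at visit 12.1 (days 168-350). For subjects boosted at visit 12.1 the latest scheduled pre-boost ELISPOT sample is therefore Day 168, which can precede the boost by up to about 350 − 168 = 182 days. Group 2 is boosted at the Day 168 visit (+/- 14 days), where research bloods are scheduled.

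**The case against.** The strongest defence is that Statistical Methods should be read with the paragraph before it, which disclaims statistical significance. On that reading the sentence excludes only hypothesis tests, and a descriptive comparison still meets sections 2 and 7. This is probably what was intended, but the sentence says comparison, not testing, so the text still needs correcting.

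Several other objections stand and limit the point:

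- **The reason is not simply wrong.** A reader might infer that the sample-size argument is mistaken altogether. For a between-group test it is sound, as the 1.2 SD figure shows. It is too broad only because it does not separate testing from estimation.
- **The boost is not part of the selection decision.** A reader might infer that both contrasts serve to choose the efficacy-trial population. The Rationale ties only the ARV contrast to that choice. It also sets no decision rule and does not say that this trial alone will decide.
- **Selection error comes from the sample size.** At a true gap of 0.5 SD the observed order of the group means is reversed with probability Φ(−0.5/0.408) = 11%. That rate is the same whether or not an interval is reported. An interval shows the uncertainty but does not reduce it.
- **Model details are not a protocol defect.** The scale, any covariate adjustment and the form of the estimate commonly belong in an analysis plan. Adjusting for Day 0 is also not a neutral choice, because the groups are not randomised and differ by design in ARV use and in viral load and CD4 nadir criteria.

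**Conclusion.** The point holds as an internal contradiction of moderate severity. Sections 2 and 7 commit to a comparison by ARV status, the Rationale gives it a purpose, and section 10 says it cannot be made. The sample size justifies forgoing formal tests: 80% power only at about 1.2 SD. It does not justify forgoing estimates: the interval half-width is about 0.85 SD for the group difference, and 0.42 to 0.64 SD of the paired difference for the boost with 24 down to 12 pairs.

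The textual conflict needs no assumption. The power figures assume two-sided 0.05 and 80% power, and the fold ranges assume a log10 SD of 0.3 to 0.6; none of these values is in the protocol. A reader might go on to infer that 24 subjects is the wrong number. The documents do not support that, since the total is offered for a descriptive safety study. The primary objective is safety and is untouched.

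**What to change.** Replace the sentence under Statistical Methods with wording such as:

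> No formal hypothesis testing. For the secondary objectives, the between-group difference in the ex-vivo interferon-gamma ELISPOT response to antigen 85A at one pre-named visit after the first vaccination, and the within-subject change after the second vaccination, will be estimated with 95% confidence intervals and labelled exploratory.

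Then:

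- State that the ARV contrast is not randomised. Placing it after the first dose also avoids the different boost timing in the two groups.
- Reword the Rationale so that the choice of a group for an efficacy trial is hypothesis-generating.
- State that for Group 1 subjects boosted at visit 12.1 the pre-boost reference is the Day 168 sample, and that the paired n may be below 24.

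The visit is the trial team's choice; what matters is naming it in advance. The cost is protocol wording and a few lines of analysis on samples already scheduled. The downside is that the intervals will be visibly wide.
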